**Data analysis plan**

Aim1: All interviews conducted in local language (Malayalam) will be simultaneously translated to English and transcribed. Interviews conducted in English language will be transcribed. The data analysis will follow a framework method of analysis
^
55
^. After the data is transcribed, the transcripts will be read line-by-line to get familiarised with the data. First a few transcripts will be coded using an inductive method. Later, a working analytical framework will be generated by merging the initial codes. The working analytical framework will then be used to index the remaining interviews. After indexing all the interviews, key themes will be generated by merging categories having similar meaning for each stakeholder. Finally, the data will be interpreted based on the convergences and divergences between the data themes across different stakeholders.

 Aim 2: All quantitative analysis will follow guidelines of cluster randomised trials
^
56
^. We will employ intention to treat analysis except in the sub-group analyses. Initially, baseline characteristics will be compared by treatment group to examine the adequacy of randomisation. The primary analysis will be a complete case analysis. However, missing data on outcome variables will be reported and sensitivity analyses will be conducted after multiple imputation of missing data.

The DAOH will be calculated by subtracting days in hospital and days from death until end of study follow-up from the total follow-up time of 730 days. The DAOH is a patient-centred outcome, which accounts for multiple events over the two-year course of a study period, weighs death more than hospitalisation, and deaths occurring early more than those occurring later. Empirical density curves will be created to show the distribution of DAOH over two-year follow-up period, stratified by intervention group. The median and the interquartile range of DAOH by treatment group will be provided. Poisson regression with a robust variance estimate
^
57
^ and an offset term to account for clustering will be employed in the analyses of DAOH per two-years of follow-up time. This procedure will yield a rate ratio and 95% CI
^
57
^. The rate ratio is the DAOH in the intervention arm divided by DAOH in the enhanced usual care arm. A rate ratio of >1 indicates more DAOH in the intervention arm in comparison to the usual care arm (i.e., favours the intervention).

Multilevel mixed-effects survival models will be employed for analyses of time to secondary outcomes (composite of mortality and hospitalisation). A random term identifying the location of participating sites will account for the clustering effect. We will also conduct a landmark analysis conditional upon intervention group membership at 30 days of follow-up. The between-group differences for each of the secondary outcomes (other than binary outcomes variables) will be measured using mixed-effect linear models and after accounting for clustering of observations. Standard errors will be calculated using robust estimation procedures
^
58
^.

Pre-specified sub-group analyses (age group, sex, region, type of facility, clinical severity) will be conducted. The significance of subgroup effects will be assessed by tests of interactions of covariates and the treatment effect.

Finally, as an exploratory analysis we will also use win ratio
^
59
^ to analyse the composite secondary outcome of mortality and hospital admissions. The win ratio statistic prioritises the mortality and hospitalisation endpoints through sequential comparisons. Patients in the intervention and usual care group will be converted into matched pairs based on their baseline risk profiles. The intervention patient will be labelled as a ‘winner’ or a ‘loser’ depending on who died first. If there is no death, the pairs will be labelled a ‘winner’ or ‘loser’ depending on who had a hospitalisation first. Otherwise, they are considered tied. Finally, the win ratio will be generated, which is the total number of winners divided by the total numbers of losers. A 95% confidence interval and
*P*-value for the win ratio will be obtained. If matched pairs are not possible; the analyses will be conducted on unmatched pairs.

The data on costs for the intervention and control groups will be compared to assess Incremental Cost-Effectiveness Ratios (ICER), the differences in outcomes between the intervention and control groups versus differences in costs of the intervention components. ICER measures will include the cost per case of primary outcome avoided. If the primary clinical outcomes are shown to differ significantly between group, a full economic evaluation of the lifetime costs, benefits, and cost-effectiveness (in life years gained) comparing the usual care to intervention strategy will be performed. Decision models from health system and societal perspectives, a lifetime analytic horizon, and 3% discounting of future costs and outcomes will be used. QALYs will be derived from EQ5D-VAS. We will also estimate the economic rate of return of an additional rupee spent on the intervention, with the return being in the form of knock-on costs of health services saved. For this purpose, the costs of the intervention will be the direct and indirect costs for the intervention components but excluding knock-on costs on health service use. The differences in the costs of health service use in the treatment and control participants will be used to construct an estimate of monetary savings. The ratio of these (discounted using 3%) savings and intervention costs, will be used to derive the economic rate of return over 2-years from the start of the intervention.

Aim3: All interviews conducted in local language (Malayalam) will be simultaneously translated to English and then transcribed by the post-doctoral and doctoral level fellows engaged in the study. Interviews conducted in English language will be transcribed. Field notes will be collected as part of process evaluation. Qualitative analysis will be done using a thematic analysis. A deductive coding approach will be done using the Normalisation Process Theory (NPT)
^
60
^, which will help to determine factors that promote or inhibit the incorporation of interventions into routine work. The findings will be interpreted using components of the RE-AIM
^
61
^ (Reach, Efficacy, Adoption, Implementation and Maintenance) framework to help inform the adoption, likelihood of adoption and key predictors of integrating and continuing the new care model.

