Caregivers of patients with HF	In-depth interview Total 10–12 IDIs	● Perceptions and behaviours on clinical management, lifestyle, and self-care ● Feedback on proposed intervention components and methods ● Gauge caregivers’ interest and acceptability
Physicians Nurses Dieticians Physiotherapists	In-depth interview 10–12 interviews in each category (30–36 total interviews)	● Perceived quality of HF care ● Perceived patient barriers and facilitators to delivery of care, lifestyle change, and self-care ● Gauge feasibility of planned intervention components

**
*Collaborative care model intervention (Aim 2)*
**

A parallel group cluster RCT of more than 1500 adult HF patients with reduced ejection fraction from 22 units in India
^
36
^ will be used to address Aim 2. Each participating unit will be randomly assigned to one of two arms: 1) those delivering a comprehensive CCM (intervention) or 2) those delivering standard of care (usual care).

The selected hospitals will be independent units with dedicated staff employed at each site for recruitment and follow-up of patients included in the trial. The site teams will have similar compositions in terms of clinical roles.

Cluster eligibility criteria: Eligible units will include HF centres of major hospitals from the national heart failure registry or Kerala heart failure registry that serve ≥80 new patients in six-months and consented to the randomisation plan. All HF patients will also be required to provide individual consent to participate in the study.

Patient eligibility criteria and randomisation: Potential participants must meet the standard definition of HF
^
37
^ (HF with reduced ejection fraction of <40%) based on echocardiography to be eligible to enter the study. Consecutive patients will be recruited from the participating centres. Eligible units will be randomised at one time point, prior to trial implementation. The allocation ratio will be 1:1. Randomisation procedures will not be blocked, restricted, or matched. We will use computer generated random numbers to allocate half of the units to each arm of the study.

*Duration of treatment period and follow-up*

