**Trial sample size and power**

The mean difference in DAOH was assumed to be 20 days (586 Vs 566 days with a standard deviation of 69 days) at two-year. We used the DAOH at two-year from the Trivandrum Heart Failure Registry in the sample size calculation
^
7
^. In the intervention group, we assumed 3% higher DAOH. A sample size of 770 HF participants per group (a total of 1540), in 11 equal clusters per arm (total 22 clusters) provides 91% power for a 2-sided 5% alpha. Assumptions; an ICC of 0.01 (design effect 2.08), coefficient of variation of cluster size of 0.85.

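### The plan exempts subgroup analyses from intention to treat without giving a reason or a replacement population, although the listed factors are compatible with analysis by randomised arm

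*Protocol article*

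**What the plan says.** Randomisation is by hospital: "Each participating unit will be randomly assigned to one of two arms" (Study design approach, Aim 2). The Data analysis plan for Aim 2 then sets the analysis population: "We will employ intention to treat analysis except in the sub-group analyses". Shortly afterwards it adds: "The primary analysis will be a complete case analysis". Sensitivity analyses after multiple imputation are to follow.

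Later in the same section come the subgroups: "Pre-specified sub-group analyses (age group, sex, region, type of facility, clinical severity) will be conducted". Inference is by interaction: "The significance of subgroup effects will be assessed by tests of interactions of covariates and the treatment effect".

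Nothing else in the article explains the exception, names a per-protocol, as-treated or other population for the subgroups, or brings the interaction tests back under intention to treat.

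**The concern.** Intention to treat and subgroup analysis do not conflict. Splitting patients by a baseline characteristic leaves each of them in the arm to which their hospital was allocated, so a subgroup contrast can still compare randomised arms. An express exemption gives that up with no visible gain.

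This is more than detail left to a statistical analysis plan. The protocol states a rule. An analysis plan that kept intention to treat for subgroups would contradict the protocol, and one that followed the protocol would have to choose some other population. The trial is open label, and under Data entry and data management the study fellows both clean and analyse the data, so that choice should not be left open.

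What is at stake is the reading of the subgroup results. If patients can be dropped or moved after allocation, an apparent difference between, say, two types of facility could reflect who was kept in the analysis and not how the intervention worked. The subgroup estimates would also no longer break down the overall estimate they are meant to qualify.

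**Working it through.** The plan states no figure for this point, so there is none to reproduce. The check is a comparison of the plan's statements, followed by an illustration on assumed inputs.

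**1. Do the factors need an exception?**
- Region and type of facility are most naturally properties of the hospital, known when it is randomised.
- Age group and sex are patient characteristics at entry.
- Clinical severity is naturally read as baseline severity, although the plan does not say when it is taken. If it were taken during follow-up, the remedy would be to redefine the subgroup, not to leave intention to treat.

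None of the five requires leaving the randomised comparison.

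**2. Does the interaction test suggest a restricted population?** No. A treatment-by-covariate interaction test uses patients at every level of the covariate, in both arms. Nothing in the subgroup sentences mentions adherence, exposure or exclusion.

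**3. What could go wrong if the exemption were used?** Within one subgroup level, let a share *f* of an arm be excluded, and let the excluded patients average *g* fewer days alive and out of hospital (DAOH) than those kept, whose mean is *K*.
- Full arm mean: (1 − f)·K + f·(K − g) = K − f·g.
- Mean after exclusion: K.
- Shift in the arm mean: f·g.

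The document gives neither *f* nor *g*. Over an assumed range:

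| f | g = 25 days | g = 50 days | g = 100 days |
|---|---|---|---|
| 5% | 1.25 | 2.5 | 5 |
| 10% | 2.5 | 5 | 10 |
| 20% | 5 | 10 | 20 |

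**4. From arm mean to interaction.** The arm-mean shift is not itself the bias in an interaction.
- Bias in the treatment contrast within a level: b = f₁g₁ − f₀g₀ (intervention minus usual care).
- Bias in the interaction between levels A and B, in days: b_A − b_B.

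Examples, all with assumed inputs and g = 50 days:
- 20% excluded from both arms of a level: b = 10 − 10 = 0.
- 20% excluded from the intervention arm only, at both levels: b_A − b_B = 10 − 10 = 0. Each subgroup contrast is shifted by 10 days, but the interaction is not.
- Intervention arm only, 20% at level A and 5% at level B: 10 − 2.5 = 7.5 days.

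The third example gives 5 − 1.25 = 3.75 days with g = 25 and 20 − 5 = 15 days with g = 100. Exchanging the levels, or letting the excluded patients do better than those kept, reverses the sign. The planned model gives rate ratios, so on that scale the shifts cancel when they are equal in proportion and not in days. The principle is the same.

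For scale only, the sample size section says: "The mean difference in DAOH was assumed to be 20 days (586 Vs 566 days with a standard deviation of 69 days) at two-year". That 20-day figure belongs to the primary comparison, which the exception does not touch.

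**The case against.** The strongest reply is that the sentence is loose wording. Intention to treat means analysing the whole randomised set, a subgroup is part of that set, and the authors may have meant no more than this. The pre-specified factors and the interaction tests fit that reading. It cannot be ruled out, but it does not rescue the sentence: an interaction test does use the whole set, so the exception is still misplaced and needs the same correction.

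A second reply is that as-treated analysis has little room here. Under Study intervention overview, all patients at an intervention hospital receive the collaborative care model and all at a usual-care hospital receive standard care, so allocation and care received coincide by design. This stands, and it makes exclusion after allocation the more realistic route to bias than reclassification. No such exclusion is proposed anywhere in the article.

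A reader might go further and infer that the subgroup effects will be computed on non-randomised comparisons, that exclusions would necessarily be one-sided because only intervention patients can be non-adherent, and that the bias would be a large share of the target effect. The documents do not support this. No replacement population is named, so a biased comparison is permitted but not certain. Use of the mobile application exists only in the intervention arm, but medication adherence is scheduled at follow-up visits with no restriction by arm, and application use is nowhere made an analysis criterion. Any figure in days rests on assumed inputs, and a shift in one arm's mean is not the bias in an interaction.

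Finally, subgroup analyses are secondary, and an article may leave analysis-set definitions to a fuller document. That limits the weight of the point. It does not excuse a rule that is stated and unfounded.

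**Conclusion.** Wrong as written. The plan exempts subgroup analyses from intention to treat with no reason and no replacement, for factors that appear to be baseline characteristics and can be analysed by randomised arm. The rule permits exclusion or reclassification after allocation. If that differs by arm and across subgroup levels, interaction tests would mix effect modification with selection, and subgroup results would refer to a different population from the overall result.

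The size and direction of any bias cannot be computed from the document. The illustrative interaction shifts of 0 to 15 days rest wholly on assumed exclusion shares and prognostic gaps, and show only that the effect may be nil or appreciable. The conclusion assumes that clinical severity is meant as baseline severity. The primary analysis is unaffected.

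**What to change.** Delete the clause that carves subgroup analyses out of intention to treat. Add a sentence to this effect: *Subgroup and interaction analyses keep each patient in the arm to which their hospital was randomised and use the same analysis set as the corresponding overall analysis. Any per-protocol subgroup analysis is supplementary and labelled as such.*

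The wording should stay this narrow. A blanket statement that every analysis uses every patient would conflict with the complete-case primary analysis and with the landmark analysis at 30 days, both set out in the same section.

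The cost is a small text amendment, carried into the statistical analysis plan. It needs no new data, no change in trial conduct and no change to the sample size.

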We will conduct a rolling recruitment over a period of six-twelve months. Each patient in the study will be followed-up for a period of two years from the date of recruitment. The first follow-up visit in the intervention arm will be conducted on the seventh day. Additional two follow-up visits for clinical status occurs at an interval of three-months. Participants are subsequently seen no less than every six months. Regardless of the treatment group assigned, we will follow-up all study participants in this manner (assessment at 7-th day will be only in the intervention arm) until study completion.

*Measurements in the study*

A structured questionnaire
^
38,
39
^ will be administered by trained research nurse to collect relevant data at baseline, and every three months until two years from baseline. At these visits, interval assessments of HF and angina symptom status, current use of medications, and clinical endpoint data including hospitalisations and procedures since the previous visit will be documented (
Table 2). The baseline questionnaire includes assessments of demographic and socio-economic variables, general health status, aetiology, history and risk factors, diet pattern, physical activity, tobacco, and alcohol consumption, quality of life, and six minutes walking distance. Depression and anxiety scores will be collected from each participant by using Patient Health Questionnaire- 9 (PHQ-9)
^
40
^ and Generalized Anxiety Disorder Questionnaire (GAD-7) at baseline and during follow-up visits
^
41
^. Medication adherence will be measured using four item Morisky Green Levine medication adherence scale during the follow-up visits
^
42
^. The follow-up study questionnaire will also assess the patient satisfaction in quality of care, and family support.

**Table 2. T2:** Study measurements in TIME-HF.

Study measurements	Method/Instrument
Blood pressure in mmHg	Electronic BP monitor
Height in cm	Stadiometer
Weight in kg	Digital weighing scale
Waist circumference in inches	Non elastic measuring tapes
Etiology and risk factors	Details of the etiology and risk factors using a questionnaire
Investigations	Blood reports, ECHO, ECG reports
Current Medication	Details of all medications the patient was taking at the time of contact
Depression	PHQ-9 ^ 40 ^
Anxiety	GAD-7 ^ 41 ^

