**Figure 1. f1:**
[figure not shown]
Collaborative care model (CCM) interventions in TIME-HF trial.

Two linked mHealth applications (patient and nurse applications) will be developed exclusively for the trial. The nurses, doctors and patients involved in the study will get customised access to the mHealth application. The mHealth application will allow for real time communication between the patients and the concerned nurses in the study. Nurses will be able to communicate also with the treating physician through the application. The mHealth patient application will be made available in Google Play. During the recruitment, the patient application will be installed in the patient’s phone. The concerned nurse will be able to generate a secure secret code with the help of their mHealth application, which will be essential to formally onboard the patient in the mHealth application.

The patient application will be enabled with options to update risk factors, anxiety levels, depression, and warning signs and symptoms of HF. Further, there will be options to send images, text, and voice messages. Every week the mHealth application will push a weekly survey instrument to the patient, which will cover interval assessments of HF, activities of daily living, and warning signs and symptoms. Based on the severity of the signs and symptoms reported, the application will generate amber and red alerts to the nurses. The nurses will be required to respond to those alerts immediately using their mHealth application based on the severity of the alerts and the reaction time to respond to those alerts will be documented. There will be options to modify the prescription of the patient through the mHealth application. Although the nurses can initiate the prescription change and recommend modifications, it will require approval from the treating physician. Once approved by the treating physician, the new prescription will automatically get updated in the patient application. The patients will be able to download the modified prescription using their mHealth application.

The intervention will consists of three phases (

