**Study outcomes**

Primary outcome is the days alive and out of hospital (DAOH) during the two-year follow-up period. Major secondary outcomes include; a) a composite endpoint of mortality (all-cause) or hospitalisation (>24 hours) during study follow-up period, b) six minutes walking distance, c) adherence to GDMT and d) quality of life.

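### The complete-case primary analysis of DAOH keeps recorded deaths but drops patients lost alive, so unequal loss between arms can bias the rate ratio in either direction

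*Protocol article*

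**What the plan says.** Four statements in the protocol article bear on this point.

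- **Principle** (Data analysis plan, Aim 2): "We will employ intention to treat analysis except in the sub-group analyses".
- **Primary analysis set** (same paragraph): "The primary analysis will be a complete case analysis". The next sentence gives the mitigation: "However, missing data on outcome variables will be reported and sensitivity analyses will be conducted after multiple imputation of missing data".
- **Outcome** (next paragraph): DAOH is obtained by "subtracting days in hospital and days from death until end of study follow-up from the total follow-up time of 730 days".
- **Data capture** (Measurements in the study): at each visit, "clinical endpoint data including hospitalisations and procedures since the previous visit will be documented".

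On contact with patients, the section on duration and follow-up gives both arms the same schedule apart from a day-7 visit held only in the intervention arm. The app belongs to the intervention: "Every week the mHealth application will push a weekly survey instrument to the patient". Usual-care sites have a clinical coordinator who captures data.

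**The concern.** For many outcomes a complete-case analysis is a tolerable default. For DAOH on a fixed base of 730 days it builds the outcome into the inclusion rule. Take two patients last seen at day 100. If one is recorded as having died that day, the remaining 630 days are known to be zero and the patient counts. If the other simply stops attending, the remaining 630 days are unknown and the patient is excluded. The complete cases then hold too many recorded deaths, and the excess grows with the amount of loss. If loss differs between arms, so does the distortion, and it passes into the primary rate ratio.

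The multiple imputation that would address this is planned only as a sensitivity analysis, so the headline result remains exposed.

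**Working it through.** The plan gives no figure for loss or for its effect, so there is none to reproduce. The yardstick is its assumed difference, 586 − 566 = 20 days, a ratio of 586/566 = 1.035 (Trial sample size and power).

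**1. Dropout unrelated to death, no true effect**

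Inputs:
- T = 730 days (Data analysis plan).
- Two-year mortality p = 1 − 2^(−2/3.7) = 0.3125, from the median survival of 3.7 years in the Introduction. The constant hazard is an assumption.
- Assumed hospital days: 10 for patients who die, 20 for survivors.
- Assumed dropout c = 5%, 10% or 15%. This is the probability of dropping out by day 730 in the absence of death, at a constant rate.

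Formulas:
- λ = −ln(1−p)/T, μ = −ln(1−c)/T, a = λ + μ.
- Kept as recorded deaths: Kd = (λ/a)(1 − e^(−aT)), with mean death day m.
- Kept as survivors: Ks = (1−p)(1−c).
- Complete-case mean = [Kd(m − 10) + Ks × 710] / (Kd + Ks).

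| Dropout c | Kd | m | Ks | Complete-case mean | Shift |
|---|---|---|---|---|---|
| 0 | 0.3125 | 342.3 | 0.6875 | 592.0 | 0 |
| 5% | 0.3051 | 339.2 | 0.6531 | 588.7 | −3.2 |
| 10% | 0.2976 | 335.9 | 0.6188 | 585.3 | −6.7 |
| 15% | 0.2899 | 332.5 | 0.5844 | 581.5 | −10.5 |

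False difference between arms:
- 5% versus 10%: 588.7 − 585.3, about 3.5 days before rounding, 17% of 20. The false ratio is 588.7/585.3 = 1.006.
- 5% versus 15%: 588.7 − 581.5 = 7.2 days, 36% of 20. The false ratio is 588.7/581.5 = 1.012.
- With p = 0.20 the same formulas give 634.1, 631.6 and 629.0, so about 2.4 and 5 days.

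The mean falls because a patient lost at day t has already survived to t and has only 730 − t days left in which to die. At c = 5%, the lost make up 1 − 0.3051 − 0.6531 = 0.0418 of patients. Of these, (0.3125 − 0.3051)/0.0418, or about 18%, die by day 730, against 31% overall.

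**2. Dropout related to death, no true effect**

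Let S and D be the mean DAOH of survivors and of those who die, and ls and ld the fractions lost in each group. Then:

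observed mean = [(1−p)(1−ls)S + p(1−ld)D] / [(1−p)(1−ls) + p(1−ld)]

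Assume S = 715 and D = 300 or 365, with p = 36% or 43% chosen to give the plan's mean of 566. The table shows the bias for the arm with more loss.

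| Who is lost | 5% vs 10% | 5% vs 15% |
|---|---|---|
| Only patients who survive to day 730 | −8.7 | −18.5 |
| Same mortality as the whole arm | 0 | 0 |
| Patients who die are lost 2 to 3 times as often | +3.5 to +6.5 | +7.4 to +13.8 |

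The sign therefore turns on how often the lost go on to die, which complete cases cannot show.

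**The case against.** **Intention to treat.** A reader might infer a flat contradiction. Many statisticians use the term for analysing patients in their allocated arm and treat missing outcomes separately. On that reading the two sentences can coexist. The conflict holds only if the term means all enrolled patients.

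**Who is dropped.** A reader might infer that only survivors are removed and that every death gives a complete DAOH. The documents support neither. The excluded are patients last known alive, and some will die unrecorded. A death completes the value only if it is ascertained and the hospital days since the last visit are known, since those are collected by looking back at visits.

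**Direction.** A reader might infer a bias in favour of the intervention. The app and the day-7 visit could improve retention there, but scheduled visits are otherwise common to both arms and each site has dedicated follow-up staff. Higher loss in usual care is conjecture, and the sign can reverse.

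**Size.** Assuming that no lost patient dies gives larger figures. With 31% mortality, means of 245 and 710 days, and fraction l of survivors lost, the mean is [0.31×245 + 0.69(1−l)×710] / [0.31 + 0.69(1−l)]. This gives 560.7, 555.2 and 549.2 at 5%, 10% and 15%, hence 5.5 and 11.5 days. These are upper illustrations.

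The plan's SD of 69 days also points to smaller effects. In step 1 the gap between survivors and patients who die is 710 − 332.3 = 377.7 days. This alone implies an SD of 377.7 × √(0.3125 × 0.6875) = 175. Capping the SD at 69 limits the gap to 69/0.4635 = 149 days. The share of deaths among complete cases is 0.3184, 0.3247 and 0.3316 at 5%, 10% and 15% dropout, so the false difference would be about 0.9 and 2.0 days. That gap would require patients who die to average about 710 − 149 = 561 days, which fits poorly with the Introduction's one in five dead within three months. The dependence of the size on this spread nevertheless stands.

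**Inferred rule.** The article does not say outright that a patient lost at day 100 is excluded, and it mentions an offset and follow-up time. But the offset is described as handling clustering, and exclusion is the ordinary meaning of complete case for an outcome with a fixed 730-day base.

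**Conclusion.** The point holds as a defect in a stated primary-analysis rule, not as a missing detail. Followed as written, the rule selects patients partly by outcome. Dropout unrelated to death does not make it harmless: it pulls the mean down more in the arm with more loss. With 31% two-year mortality the false difference is about 3.5 days (5% versus 10% dropout) to 7 days (5% versus 15%); with 20% mortality it is about 2.5 to 5 days. It is smaller if DAOH really varies as little as the plan's SD implies.

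Mortality shape, dropout rates and hospital days are assumptions. Equal loss with equal risk in both arms gives no false difference. If the lost are at clearly higher risk of death, the bias shrinks or favours the arm with more loss. No claim about which arm benefits is supported. The planned imputation softens the problem but does not protect the primary estimate. The change should be made; it does not call the design into question.

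**What to change.** Exchange the roles of the two planned analyses, before any comparison by arm is seen:

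- **Primary:** all enrolled patients in their allocated arm. Use the days observed, and multiply impute the unobserved days of patients lost alive. The imputation model should include hospital, arm, baseline risk and days already observed.
- **Ascertainment:** seek vital status at day 730 for every patient, including those who stopped attending, by the same procedure in both arms.
- **Sensitivity:** keep complete case here.
- **Reporting:** give the number lost while last known alive, by arm.
- **Wording:** state that intention to treat means all enrolled patients as allocated.

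The cost is a change of wording, some effort to trace vital status, and slightly more analysis work, since the imputation is already planned. The small downside is that the primary result then relies on the imputation model and its missing-at-random assumption. Wider vital-status ascertainment reduces that reliance.
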